### Covariates

To account for non-random SEN provision assignment, we will use information on several covariates that are known or suspected to be associated with SEN provision and hospital contacts based upon prior literature. These include CLP specific influences, further clinical/birth, socio-demographic, geographical, and educational influences. See
Table 5 for a list of potential confounders from relevant literature. The distribution of these potential confounders by exposure status will be examined (see
Table 5 for an outline) and directed acyclic graphs representing the assumed relationships among these variables, SEN exposure, and the outcome of interest will be drawn to identify the variables that will be controlled for to estimate the causal effect of the interventions, using the opensource software,
DAGitty ver 3.0.

**Table 5. T5:** Socio-demographic, educational and health characteristics by recorded SEN categories. The table will include means with standard deviations or numbers and row percentages as appropriate, Cleft Lip and/or Palate derived population.

		SEN provision in January Year 1		
Covariate Group	Covariates	None	SEN support	EHCP
**Clinical**	**Cleft severity**			
	Cleft Lip Only			
	Cleft Palate Only			
	Unilateral Cleft Lip and Palate			
	Bilateral Cleft Lip and Palate			
	**Maternal age (years)**			
	**Gestational age (weeks)**			
	**Comorbidities**			
	Mental Behavioural			
	Cancer Blood			
	Chronic infections			
	Respiratory			
	Endocrine Metabolic Digestive Renal Genitourinary			
	Musculoskeletal Skin			
	Neurological Sensory			
	Cardiac conditions			
	**Pre-follow-up: Rate of pre-follow-up outpatient visits (per 1,000 years)**			
	**Pre-follow-up: Rate of pre-follow-up AE visits (per 1,000 years)**			
	**Pre-follow-up: Rate of pre-follow-up Admitted Patient Care visits (per 1,000 years)**			
**Educational**	**Academic cohort (Year 1)**			
	2008/2009			
	2009/2010			
	2010/2011			
	2011/2012			
	2012/2013			
	2013/2014			
	2014/2015			
	2015/2016			
	2016/2017			
	2017/2018			
	2018/2019			
	**Month of birth**			
	Jan			
	Feb			
	Mar			
	Apr			
	May			
	Jun			
	Jul			
	Aug			
	Sep			
	Oct			
	Nov			
	Dec			
	**Early years foundation school profile (z-score)**			
	English			
	Mathematics			
	**Free school meal eligibility**			
	Eligible			
	Not Eligible			
	**School level information: % of SEN**			
	None			
	SEN			
	EHCP			
	**School level information:** **Pupil teacher ratio**			
**Socio-economic**	**Ethnicity** **latest recorded in NPD**			
	Asian Asian British			
	Black Black British Caribbean African			
	Mixed or multiple ethnic groups			
	White			
	Other			
	**English as a first language**			
	Recorded as English			
	Not recorded as English			
	**Income deprivation affecting children index quintile**			
	Most Deprived - 1			
	2			
	3			
	4			
	Least Deprived - 5			
**Outcomes** ** (health)**	**Follow-up: Rate of post-entry days in AE (per 1,000 years)**			
	**Follow-up: Rate of post-entry days in Admitted Patient Care (per 1,000 person-years)**			
	**Follow-up: Rate of post-entry days in APC OR AE (per 1,000 person-years)**			
**Outcomes** ** (education)**	**Medical related absence sessions (per 100,000 sessions)**			
	**Unauthorised absence sessions** **(per 100,000 sessions)**			

Specifically, these covariates, measured at birth or before or at the start of Year One, include: cleft severity (based upon prior literature - (
Fitzsimons *et al.*, 2018) – see
Table 1 for ICD10 codes to differentiate cleft severity), comorbidities (categories based upon prior literature (
Hardelid *et al.*, 2014)), gestational age, maternal age, prior hospital contact (unplanned, and outpatient contacts), gender, ethnicity (latest recorded in NPD to reduce missingness), English as a first language, Income Deprivation Affecting Children Index (IDACI) quintile, free school meal eligibility, month of birth, academic cohort (to account for changes in policy over time) and standardised school ready assessments (Early Years Foundation School Profile). Additional school-level variables we aim to include is the proportion of children in the school the child attends in Year One who were recorded as receiving SEN support/EHCP in the previous academic year, and current pupil teacher ratio. 

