## Abstract

**Background:**

Special educational needs (SEN) provision is designed to help pupils with additional educational, behavioural or health needs; for example, pupils with cleft lip and/or palate may be offered SEN provision to improve their speech and language skills. Our aim is to contribute to the literature and assess the impact of SEN provision on health and educational outcomes for a well-defined population.

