## Introduction

Special educational need (SEN) provision offers reasonable adjustments in children and young people (CYP) in an educational environment who need additional health, academic, or behavioural support. This includes children with complex health requirements or learning difficulties. SEN provision offers support to those with needs using a variety of facilities. SEN provision in the English educational setting is divided into two main categories: SEN Support (previously known as Action, Action Plus or non-Statemented SEN) and Education and Health Care Plan (EHCP, this is previously known as a statement of SEN) (
Timpson & Department for Education, 2014). SEN Support is organised by the educational environment (e.g., school or college) and provides access to children and young people in need of SEN provision, with support that may include teaching assistants who aid in communications, specialised adapted learning programmes and supporting physical needs. An EHCP is funded by local authorities for children and young people who require further adjustments and often require additional health specific resources (compared to SEN Support) to aid in education, health, and social care needs. Due to the funding and organisational streams of SEN provision, allocation of SEN provision varies over time and location, which can be impacted by changes in legislation, school governance structure and local authority (
Liu *et al.*, 2020).

Currently, there is limited research on the impact of SEN provision on academic and healthcare outcomes in populations who have a need for SEN provision. To estimate the causal effect of SEN provision on outcomes, randomised controlled trials (RCT) would have to be conducted, however such study designs are not always feasible due to the human, time, financial and ethical costs associated. As SEN provision is universally available in primary education environments (schools teaching pupils aged five to eleven years) in England, conducting an RCT would be unfeasible and possibly unethical for certain groups of children. In lieu of RCTs, observational studies provide a pragmatic, data-driven, observational alternative when trials are not possible. One major challenge with using observational data when compared to data collected from RCTs is the risk of confounding, particularly, confounding by indication whereby assignment to treatment is not random and is often related to the severity of a medical condition (

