Salas *et al.*, 1999). However, attentive study design can mitigate such biases in observational data by emulating the protocol of an equivalent RCT (
Hernán & Robins, 2016).

An observational dataset that can be used to estimate the causal effect of recorded SEN provision on healthcare outcomes is the ECHILD dataset (
Mc Grath-Lone *et al.*, 2022). The ECHILD dataset is the first dataset in England of linked academic data (National Pupil Database - NPD) with secondary care hospital data (Hospital Episode Statistics - HES) for all pupils educated in state funded schools, and has been used to investigate the associations between health, education and social care (
Mc Grath-Lone *et al.*, 2022). Therefore, the ECHILD dataset provides the opportunity to conduct observational studies with long-term follow-up with current follow-up being up to age 25 years (from birth in 1995 until hospitalisations in 2020). With data on clinical diagnoses, social care contacts, hospital visits, academic attainment, school absences and SEN provisions in school, the ECHILD dataset enables adjustment for different confounders in populations at risk and to focus on specific populations at risk, identifiable from the linked hospital data, for example using phenotypes such as children with major congenital anomalies (e.g., Down Syndrome), cerebral palsy, developmental disorder of scholastic skills, epilepsy, diabetes, and premature birth. Education data in ECHILD include provision of support for SEN, free school meal status and measures of socioeconomic deprivation, as well as national examination results (at multiple key stages) and absence and exclusions from school, while health related outcomes such as (specific types of) hospitalisations are also available via linkage to hospital records.

In this study protocol, we describe how we aim to use the ECHILD dataset to design a study that appropriately emulates an RCT to address causal question of the impact of receiving alternative categories of SEN provision (including none) on unplanned hospital utilisation and school absences in children who were born with cleft lip and/or palate (CLP). Incidences of CLP are identified in 900 new-borns in England yearly and impact communications (hearing and speech), dental health (
Gallagher & Collett, 2019) and psychosocial health. CLP is associated with reduced academic attainment (

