### Dataset and linkage

The data source we propose is the ECHILD database, a pseudo-anonymised dataset that links the National Pupil Database (NPD) with Hospital Episode Statistics (HES). In brief, the ECHILD's extract of the NPD contains data from academic terms (Summer, Autumn, and Spring) between 2006 and 2020 and contains information on (but not limited to) school, local authority, year/month of birth, gender, ethnicity, first language, socioeconomic status, free school meal status, absence related data, social care/children in need related data and SEN provision.

The ECHILD’s extract of HES contains details on accident and emergency attendance, admitted patient care, critical care, and outpatient appointments between 1997 until 2021. It contains details on birth admissions, sex recorded by physician, ethnicity, clinical information recorded during hospital admissions, including details of diagnoses, and operations. HES covers 99% of public hospital activity in England (
Herbert *et al.*, 2017). HES records since 1998 are also linked to ONS Mortality data covering information on causes and timing of deaths. The linkage coverage periods are described in
Mc Grath-Lone *et al.* (2022). ECHILD has been shown to have a linkage rate between NPD and HES of 95%; the high linkage rates are attributable through a two-stage linkage process (
Libuy *et al.*, 2021).

Full methodology of creating the ECHILD dataset is described by
Mc Grath-Lone *et al.,* 2022. Enquiries to access to the ECHILD dataset is obtainable by contacting
[contact]; all researchers accessing the ECHILD dataset will need to be an Office of National Statistics (ONS) accredited researcher. Access to the ECHID dataset will be made through the ONS Secure Research Service, a trusted research environment which requires the researcher’s institution to have Assured Organizational Connectivity, Population

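### Hearing and speech need, a reason the plan gives for SEN provision in cleft pupils, is adjusted for only through broad proxies, so residual confounding by indication is likely and its size is unknown

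*Protocol article*

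**What the plan says.** The Abstract gives an example of why SEN is provided in this population: "pupils with cleft lip and/or palate may be offered SEN provision to improve their speech and language skills". The Introduction says that clefts "impact communications (hearing and speech), dental health" and psychosocial health. It also identifies the main threat to an observational comparison as "confounding by indication whereby assignment to treatment is not random and is often related to the severity of a medical condition".

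The Covariates section and Table 5 set out the candidate confounders. Those closest to hearing and speech are:
- four cleft types, used as cleft severity;
- eight comorbidity groups, one of them "Neurological Sensory";
- the school-readiness score, listed as "Early years foundation school profile (z-score") and broken down into English and Mathematics;
- prior hospital use. The text has "prior hospital contact (unplanned, and outpatient contacts), gender, ethnicity (latest recorded in NPD to reduce missingness), English as a first language"; Table 5 shows three separate pre-follow-up rates, for outpatient, A&E and admitted care, none split by specialty or reason.

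The final set is to be chosen with directed acyclic graphs (DAGs). Dataset and linkage says that HES holds "clinical information recorded during hospital admissions, including details of diagnoses, and operations", as well as outpatient appointments.

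**The concern.** Confounding by indication is controlled only as well as the indication is measured. Here the protocol names a need that prompts SEN, yet no candidate confounder measures it specifically. Hearing loss, speech disorder, ear operations and further palate surgery are not listed. They enter only as part of a pooled comorbidity group or an overall contact rate.

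If pupils with greater hearing or speech need are more likely to receive SEN, and that need also raises absence or hospital use, the SEN rate ratios are pushed upwards. The g-formula, inverse probability weighting and weighted regression adjustment all use the same measured covariates, so agreement between them would not reveal the problem.

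**Working it through.** **1. Stated need against listed covariates**

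| Aspect of need | Nearest listed item | What it leaves out |
|---|---|---|
| Hearing | Comorbidity group joining neurological and sensory conditions | Cannot separate hearing loss from epilepsy or a visual condition |
| Speech and language | English readiness z-score; cleft type | Attainment and anatomy, not speech |
| Ear and palate surgery | Admitted-care rate in Table 5 | Not split by procedure; the Covariates text names only unplanned and outpatient contact |
| Audiology or speech follow-up | Outpatient rate | Not split by specialty |

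The National Pupil Database fields for type of need (Table 2) cannot fill the gap for None versus SEN Support, because they are described only for pupils who already have SEN.

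**2. Whether another part of the plan covers it**

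The DAGs are to be drawn among the listed variables, SEN and the outcome, so as described they select from the list. The Causal inference section states that the main estimators assume all relevant confounders are measured. Instrumental variables depend on finding an instrument, and difference-in-difference is only raised as a possibility. The Sensitivity analyses cover delayed recording, splitting of the outcomes, and sex versus gender. None addresses unmeasured confounding.

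**3. Routes to the outcomes**

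Table 4 includes illness (code I) and medical or dental appointment (code M) sessions in the absence outcome, so a child with continuing ear or speech follow-up can accrue outcome sessions directly. For unplanned hospital days the documents state no link; a route is plausible only.

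**4. Size, for illustration only**

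The plan gives no figure to reproduce, and every input in this step is assumed. For a binary need with prevalence p1 in the SEN group and p0 in the None group, and rate ratio g on the outcome, the bias factor is B = [1 + p1(g − 1)] / [1 + p0(g − 1)].

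Treating p1 and p0 as the imbalance left after the listed covariates:
- 0.50 v 0.30, g = 1.3: 1.15 / 1.09 = 1.06
- 0.60 v 0.25, g = 1.5: 1.30 / 1.125 = 1.16
- 0.70 v 0.20, g = 2.0: 1.70 / 1.20 = 1.42
- any prevalences, g = 1: 1.00

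The first three cases raise imbalance and outcome effect together, which widens the range.

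**5. What a proxy achieves**

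Take p1 = 0.6, p0 = 0.2, g = 1.5 and 30% treated. With no adjustment, B = 1.30 / 1.10 = 1.18. Now standardise over a binary proxy with sensitivity 0.6 and specificity 0.9:
- Proxy positive: 0.40 of treated, 0.20 of untreated; need prevalence among them 0.90 and 0.60.
- Proxy negative: 0.60 of treated, 0.80 of untreated; need prevalence among them 0.40 and 0.10.
- Weight of the positive stratum: 0.3 × 0.40 + 0.7 × 0.20 = 0.26; of the negative stratum, 0.74.
- Residual: (0.26 × 1.45 + 0.74 × 1.20) / (0.26 × 1.30 + 0.74 × 1.05) = 1.265 / 1.115 = 1.13.

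A weaker proxy (0.3, 0.95) leaves 1.16 and a stronger one (0.8, 0.9) leaves 1.10. In these cases adjustment reduces the bias without removing it.

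**The case against.** The strongest reply is that the need is not left uncontrolled. Cleft severity, comorbidities and readiness scores are all in the set, and the protocol describes the readiness profile as a good predictor of SEN provision. Two children with equal contact rates can still differ on these items, and operative admissions could count in Table 5's admitted-care row. This stands. A reader might infer that the main indication goes wholly unadjusted, but the documents do not support that: they rank no indication as the main one, give speech and language as an example, and list several partial measures.

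A second reply is that no passage links hearing or speech need to unplanned hospital days, which are the outcome in both causal contrasts in Table 6. This also stands. The direct route is confined to medical-related absence.

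A third is that the list is of potential confounders, and that an article may leave code lists to a fuller document. This stands only in part. The article goes down to month of birth and pupil-teacher ratio, so the list reads as a deliberate choice of candidates, and nothing says that the DAGs will add unlisted ones. Predicting who receives SEN also differs from capturing the need that drives both SEN and the outcome.

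Finally, instrumental variables or difference-in-difference might help, but neither is assured.

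**Conclusion.** The point holds as one of likely residual confounding. The plan names speech and language as a reason for SEN, names hearing and speech as affected by clefts, assumes that all relevant confounders are measured, and lists only broad proxies for this need. The consequence is most direct for medical-related absence and plausible for unplanned hospital days.

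The size cannot be determined from the documents. The 1.06 to 1.42 range is illustrative and rests on assumed prevalences and outcome ratios for the uncaptured part. An upward direction requires that need raises both the chance of SEN and the outcome. A reader might go further and conclude that SEN will be made to look harmful on every outcome; the documents do not support that, since the proxies remove an unknown share of the bias and no effect of the need on unplanned days is stated. The point is a worthwhile, inexpensive improvement to the adjustment set and does not show the design to be invalid.

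**What to change.** Add the following, measured before Year One, to the candidate confounders, the DAG, the propensity score and the outcome models:
- HES indicators for a hearing-loss diagnosis and for a speech or language disorder diagnosis;
- HES indicators for middle-ear operations and for palate or speech operations;
- outpatient contacts split by specialty (ear, hearing and speech versus other), if the extract holds specialty;
- any communication or language component of the school-readiness profile, if the extract holds it.

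Recheck common support for each pair of SEN categories after adding them. Add a quantitative bias analysis for the need that remains unmeasured, reported separately for absence and for unplanned hospital days. Where an item is not available, state the limitation.

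The cost is a code list, a few derived variables and a few more model terms. Diagnoses and operations are described as held; outpatient specialty and a communication component are assumptions about the extract. Stronger predictors of SEN may reduce overlap, particularly if the EHCP group is small. The documents do not give that group's size, though the Outcome variables section expects very small intervention groups among children with Key Stage Two results.

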SENA SENELK SENELSE SENF SENPS SEN_ALL SENAPK SENSE	• SENA: Does a pupil have SEN - school action? • SENELK: Does pupil have SEN support? • SENELSE: Does pupil have SEN with statement or EHC plan? • SENF: Pupil SEN status • SENPS: Does pupil have SEN - Action Plus or Statemented? • SEN_ALL: Does pupil have SEN with or without statement or EHC plan? • SENAPK: Does pupil have SEN without statement or EHC plan? • SENSE: Does pupil have SEN with statement or EHC plan?
LatestSEN	Provision types under the SEN Code of Practice.
SENProvisionMajor	Pupil's major SEN provision group based on SEN provision code.
SENstatus	Provision types under the SEN Code of Practice.
SENUnitIndicator	Indicates if a pupil with SEN in a mainstream school is a member of a SEN Unit (sometimes called special class)
SpecialProvisionIndicator	Indicates if a pupil with SEN in a mainstream school is a member of an SEN Unit, special class or resourced provision.

NPD = national pupil database, SEN = special educational needs

Figure 1 shows our planned Consolidated Standards of Reporting Trials (CONSORT) flow diagram for identifying the population and classifying it according to the exposure variables (categories of recorded SEN provision).

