**Follow-up** ** duration**	From: Randomization to the intervention To: the end of primary school OR loss of follow-up (e.g., emigration) OR death OR end of study	From: January Census in Year One To: the end of primary school OR loss of follow-up in NPD OR death OR end of study/end of data (for HES: 31 August 2019)
**Outcome(s)**	Unplanned hospital utilisation as defined by days in AE or APC Medical related absences as defined using half-day sessions. Unauthorised absences as defined using half day sessions	Unplanned hospital utilisation as defined by days in AE or APC Medical related absences as defined using half-day sessions. Unauthorised absences as defined using half day sessions
**Interventions to** ** be compared**	One of three categories of SEN (none, SEN, EHCP) to be delivered following randomization (between start of reception and end of Year One	One of three categories of SEN (none, SEN, EHCP) as recorded by the January census in Year One
**Causal contrasts**	The average treatment effect of initiating SEN versus non-initiating SEN at all by Year One on the number of unplanned hospital days expressed as a rate ratio. The average treatment effect of initiating EHCP versus initiating SEN by Year One on the number of unplanned hospital days expressed as a rate ratio.	The average treatment effect of recording SEN versus non- initiating SEN at all by Year One on the number of unplanned hospital days expressed as a rate ratio. The average treatment effect of recording EHCP versus recording SEN by Year One on the number of unplanned hospital days expressed as a rate ratio. These estimands will be defined for the whole population and also for the sub-populations of “treated” and “untreated” children, that is the children who were (or were not) recorded to receive the relevant intervention.

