### Analysis

**
*Explorative analyses.*
** To estimate the representativeness and external validity of the derived cohort, we will compare the following distributions against existing literature, firstly, the rates of CLP children who start Year One between 2008/09 and 2018/19 (CRANE, 2021) and secondly, previously published rates such as school academic attainment (
Fitzsimons *et al.*, 2018). 

To understand whether pupils who are recorded to have received different categories of SEN provision had the chance to be recorded with another category and therefore for the intervention levels to be comparable using the available data (i.e. to assess whether the positivity assumption could be invoked when performing casual inference (
Zhu *et al.*, 2021)), we will examine the distribution of the propensity scores for the recording of SEN support/EHCP across the subgroups of children defined by their observed characteristics. The propensity scores will be predicted using logistic regression, with the covariates mentioned above included as predictors. As there are three categories of SEN (None, SEN Support and EHCP), pairwise propensity score comparisons (
Rassen *et al.*, 2013) will be evaluated for common support between: None vs SEN Support, None vs EHCP and SEN Support vs EHCP. The robustness of the selected propensity score model would be assessed by triangulating the predicted scores with those derived using machine learning methods (such as Classification and Regression Trees) (
Lee Brian *et al.*, 2010).

**
*Causal inference.*
** Once explanatory analyses have been completed, causal inference will be conducted for pairs of interventions which have common support. To account for the distribution of our outcome, that is number of unplanned hospital contacts and number of absence sessions, we will use Poisson (or negative binomial) regression models. To account for differential follow-up time, we will use the logarithm of one of the following as offsets: days between January of Year One and end of follow-up for hospitalisation usage and total number of full sessions between January of Year One and end of follow-up for school absences. The likely clustering of pupils within local authority will be addressed either by fitting mixed effects models or by using robust inference (or both).

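### The school-level SEN support/EHCP share is not defined to leave out the index child, so a child's own Reception record can enter the propensity score; the resulting bias is small (about 1-3% for EHCP) and free to remove

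*Protocol article*

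**What the plan says.** The Covariates section (paragraph after Table 5) gives the timing of the covariate list as "measured at birth or before or at the start of Year One". It then introduces two more items as "Additional school-level variables we aim to include". One of these is a share, defined as "proportion of children in the school the child attends in Year One who were recorded as receiving SEN support/EHCP in the previous academic year". Its companion is a staffing measure, worded as "and current pupil teacher ratio". Table 5 splits the school share into None, SEN and EHCP percentages, so a separate EHCP share is planned.

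Under Analysis (explorative analyses), the score is built as follows: "The propensity scores will be predicted using logistic regression, with the covariates mentioned above included as predictors".

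In Table 6 the emulated exposure is one of three categories "as recorded by the January census in Year One". The ideal trial's intervention is "to be delivered following randomization (between start of reception and end of Year One". Eligibility in the same table is Year One in a state school, with no restriction by type of school.

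**The concern.** The year before Year One is Reception. A child who attended the same school then, and already had SEN or an EHCP recorded, is one of the pupils counted in the share. Exposure is whatever has been recorded by the January census of Year One, and the ideal trial's window opens at the start of Reception. The one-year lag therefore does not place the share before exposure.

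The share is then mechanically a little higher for exposed children, even if their schools are no different from anyone else's. Weighting that balances the observed share has to compensate: after weighting, exposed children come from schools with a lower true share than their comparators. An imbalance is created where there was none. The effect is largest for the EHCP share, because one child is a small part of a pooled SEN share but a noticeable part of a share of one to three per cent. EHCP versus SEN is one of the two contrasts in Table 6.

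**Working it through.** The plan gives no figure tied to this point, so there is nothing to reproduce. The check asks how large the artefact is and what it does to a rate ratio.

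**From the document:** the definition of the share, the separate EHCP percentage (Table 5), and the use of the covariates in the score.

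**Assumed, none of it in the document:** roll n = 120, 210 or 420; mean EHCP share q = 1%, 2% or 3%; between-school coefficient of variation 0.5; f = 80% of EHCP children already recorded at that school in Reception; exposure unrelated to the true school share; outcome rate multiplied by 1.10 per SD of the true share; 3% of the cohort with an EHCP.

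**Step 1, own contribution.** One record moves the share by 1/n: 0.83, 0.48 and 0.24 percentage points at rolls of 120, 210 and 420. The mean shift among EHCP children is d = f/n.

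**Step 2, spread of the observed share.** V = (0.5q)² + [q − q² − (0.5q)²]/(n − 1). The first term is true variation between schools and the second is binomial noise. At n = 210 and q = 2%: V = 0.0001 + 0.0195/209 = 0.000193, so SD = 1.39 points.

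**Step 3, spurious standardised difference.** SMD ≈ d/√V. At n = 210 and q = 2%: 0.381/1.39 = 0.27.

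**Step 4, effect on the true share.** Only r = (0.5q)²/V of the observed variance is true variation. Balancing the observed share moves the true share by about SMD × √r of its own SD. Here r = 0.0001/0.000193 = 0.52, giving 0.27 × 0.72 = 0.20 SD.

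**Step 5, bias.** 1.10^0.20 = 1.019, or about 1.9%.

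| n / q | SMD (formula) | √r | Shift in true share (SD) | Bias (formula) | SMD (simulated) | Simulated bias, ATE / ATT |
|---|---|---|---|---|---|---|
| 120 / 1% | 0.667/1.039 = 0.64 | 0.48 | 0.31 | 3.0% | 0.64 | 1.8% / 3.2% |
| 210 / 2% | 0.381/1.390 = 0.27 | 0.72 | 0.20 | 1.9% | 0.28 | 1.6% / 2.1% |
| 420 / 3% | 0.190/1.714 = 0.11 | 0.87 | 0.10 | 0.9% | 0.12 | about 0.9-1.0% for both |

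The simulated columns use inverse probability weighting with a logistic score. The hand formula approximates the ATT. If the rate rises with the share, the rate ratio is pulled down; if it falls with the share, the rate ratio is pulled up.

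**Variations.** With only 30-50% of EHCP children already recorded (roll 210, share 2%), the SMD is 0.10-0.17. For the SEN Support share it is 0.03-0.13. Leaving the index child out brings it to within 0.04 of zero.

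**Pooled SEN share in ordinary schools.** Assume 16% prevalence and a genuine link between school share and exposure. The standardised difference at roll 210 is then 0.26-0.38 with the child and 0.22-0.34 without.

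**Scale against precision.** The Outcome variables section gives 900 × 0.62 = 558 isolated cases a year, so at most 558 × 11 = 6,138 over eleven cohorts; 3% of that is 184 EHCP children. Even under pure Poisson variation, a standard error of 0.02 on the log rate ratio needs at least 1/0.02² = 2,500 unplanned days in that group, or 2,500/184 = 13.6 per child.

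**The case against.** The strongest reply is that leaving out the index child is a programming detail that an article may leave to the code, which the plan promises to publish. The text does not say outright that the child is counted, the two variables are only ones the authors aim to include, directed acyclic graphs will settle the adjustment set, and common support is checked pair by pair. Part of this stands: nothing is locked, and the size is small. But the definition as worded covers all children in the school. A graph selects variables and does not show that a selected variable contains the child's own record. An overlap check cannot tell an artefact of construction from a real difference.

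Four stronger readings are tempting, and the documents do not carry them.

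- **The score adjusts exposure for itself.** A reader might infer this, but one record has weight 1/n and only for children who stayed at the same school. In ordinary-sized schools the pooled share barely changes.
- **The bias reaches 6%.** That figure comes from 1.10^0.64 = 1.06, which applies an effect per SD of the true share to a difference in SDs of the observed share. Much of the observed spread is noise, so Step 4 is needed.
- **EHCP children in special schools make the EHCP contrast fail through the covariate.** No passage says that an EHCP determines the school, and Table 2's unit and special-provision flags concern pupils in mainstream schools. If 25-50% of EHCP children were in schools where nearly all pupils have an EHCP (assumed), a leave-one-out share alone would still separate EHCP from SEN Support with an AUC of 0.63-0.75. That would be real non-overlap, which the planned common-support check is there to find. Dropping the variables would hide it.
- **The current pupil-teacher ratio contradicts the timing rule.** This is weak. The rule is attached to the preceding list, and follow-up starts at the January census, so a current-year ratio need not post-date time zero. The wording is merely loose.

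**Conclusion.** The point holds as a small, avoidable flaw in a derived variable. Followed as written, the definition counts a same-school child's own Reception record, and no later step in the plan removes it. Under the assumptions above, the spurious standardised difference in the EHCP share is about 0.1-0.6 and the bias after weighting is about 1-2% (ATE) or 1-3% (ATT), always from over-correcting for the school share. For SEN Support the artefact is smaller. With fewer than two hundred EHCP children likely (if 3% have one), sampling error will probably exceed this. The plan supplies none of the school inputs, so the range shows the order of magnitude and is not an estimate. The document does not support a claim that the EHCP contrasts are seriously biased. The case for changing the definition is that the change costs nothing.

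**What to change.** 1. Define the school SEN support and EHCP shares over all other pupils of the Year One school in the previous academic year, leaving out the index child. This is a one-line change to the derivation, with no loss of data and no downside.
2. Take the pupil-teacher ratio from the previous academic year, so that it agrees with the timing stated for the other covariates. The cost is one extra lagged lookup.
3. Because any state school is eligible and the school attended might follow from an EHCP (an assumption, not a statement in the plan), report the EHCP contrasts with and without the school-level variables as a sensitivity analysis. Keep them in the main score: they are plausible confounders, and removing them or restricting the population would change what is estimated. The cost is one additional run per EHCP contrast.
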